### Data handling and statistical analyses

#### Power calculations

According to the Norwegian Medical Association, the average number of listed patients pr GP is approximately 1200. Using 1000 patient pr GP (simplicity) gives us (based on previous studies 
[4,5]) an estimate of approximately 30–40 patients with chronic headaches and 10 patients with MOH per GP.

Using previous results from studies from Akershus University Hospital 
[76] regarding number of days of medication intake per month and proportion of patients with headache more than 15 days per month before and after unstructured information about MOH, we have made an approximation of the required sample size.

Using 80% power for the detection of a similar sized difference as found in the previous study for number of days of medication intake 
[76], we would need 18 patients in each arm unadjusted and five clusters (ie. GPs) with eight patients each, to achieve significant results at the 5% level. For analysis of the proportion of patients with more than 15 days of headache, power calculations yield 30 patients or eight clusters (GPs) with eight patients each. Since the intra-cluster coefficient of correlation is not known (here estimated at 0.5 as a “worst case”) and since we don’t know the degree of carry-over of information from one group of GPs to another, we assume a sample size of 20 physicians (160 patients) to be reasonably safe. This would also give significant results at the 5% level even if only five patients per GP were included.

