[30,35,64]. In addition, the SDS score has been shown to predict likelihood of successful detoxification in a general population 
[65].

Screening and Brief Intervention (BI) is a well-known approach to identify and treat unhealthy alcohol use 
[66]. The SDS and similar scales such as the Alcohol Use Disorders Identification test, have previously been used to identify individuals at risk for addiction-related problems 
[58-63,67-69]. BI involves the use of such an identification tool followed by feedback to the identified individual as being “at risk”. The final step, in this very short and simple intervention is to give information suggesting to cut down the use of the particular substance to predecided “acceptable” levels 
[66]. BI includes clear directive advice, but focus is also on increasing patients insight and awareness regarding overuse as described in more detail elsewhere 
[66,70]. The BI method has shown promising results with both short- and longlasting reduction of alcohol intake and levels of related biochemical markers such as liver transferase levels 
[66,71-73]. Similar methods have also been successfully applied for various other addictive drugs 
[70,74,75].

We have previously reported data from an open, un-controlled study of medication overuse headache in the general population, which suggested that three out of four MOH subjects had managed to reduce their medication intake after short information 
[76]. Similar simple advice also works in clinic settings 
[77,78]. One population- and one clinic-based study suggest that MOH can be successfully managed in a primary care setting after an initial collaboration with headache specialists 
[45,79].

The common headache disorders require no high-tech investigations and may therefore be diagnosed and managed by all skilled physicians. Most headaches are therefore probably best managed in primary care. Focus on MOH in primary care is therefore important both in order to prevent MOH from developing and for early diagnosis and treatment.

We have designed a BI for treatment of MOH in primary care and planned a double-blinded cluster randomized parallel controlled trial (RCT) to evaluate effects of the intervention.

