[80,81]. However, especially among those with chronic or co-occurring headache types, diagnosing headaches is not always easy. The gold standard for making a specific headache diagnosis is an interview combined with a physical and neurological examination by a physician experienced in headache diagnostics. All patients will be diagnosed based on interviews by a GP trained and experienced in headache diagnostics also in order to avoid inter-observer variation ([name]).

Some of our data will be based on retrospective self-reports and therefore open to recall bias, although here is no reason to suspect systematic bias. In order to counteract this, we will also use headache data from prospective headache diaries 
[87]. Recent studies using a similar headache diary with written instructions before first consultation found high usefulness, acceptability and comprehensibility of the diary as well as good compliance and completeness of data 
[105,106]. We will use the headache diary for periods of two weeks. This period may seem too short for infrequent forms of headache, but in our sample of chronic sufferers this should not be a problem. In addition, a longer headache registration period may reduce compliance and cause greater interference with the cohort.

A common finding in many brief intervention studies and RCTs on alcohol use, are small reductions in alcohol consumption at follow-up also in the control group 
[73,107]. Possible reasons for this may be motivational effects of screening, sensitization to screening/measurements/follow-up, non-intended advice also in BAU group, and “regression towards the mean”. In this study we have tried to minimize most assessment effects by doing a double-blinded parallel RCT, and the screening questionnaire about medication use for headache is embedded with other questions about headache in the very short screening questionnaire. The control group will not receive the SDS screening before the three months follow-up and will therefore not be affected by this.

The SDS has not been validated against other measurements of dependency in MOH sufferers and, indeed, there is still much discussion as to whether MOH represents dependency 
[50-55,57]. Being fully aware of this, we will use the SDS score, not as an attempt to define dependency, but rather to distinguish between chronic headache subjects with and without medication overuse 
[30,35].

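### The sample size treats a before-after change from an uncontrolled study as the BI-BAU difference and subtracts nothing for change under BAU

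*Protocol article*

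**What the plan says.** The Power calculations section of the protocol article takes its inputs from one previous study. It uses that study's results "before and after unstructured information about MOH, we have made an approximation of the required sample size". The medication-days calculation is made "Using 80% power for the detection of a similar sized difference as found in the previous study for number of days of medication intake", with 5% as the significance level. Its result is that "we would need 18 patients in each arm unadjusted and five clusters (ie. GPs) with eight patients each". For the proportion of patients with more than 15 headache days, drawn from the same source, "power calculations yield 30 patients or eight clusters (GPs) with eight patients each".

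The section then takes the ICC as 0.5, which it labels a worst case. It settles on 20 GPs and 160 patients, gives the unknown ICC and possible carry-over between GP groups as its reasons, and calls this reasonably safe. It adds that five patients per GP would also be enough.

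The Background cites the same study and describes it as an "open, un-controlled study of medication overuse headache in the general population". The outcome table (Table 3) and the Statistics section make the trial's comparison one between BI and BAU at three months. The Discussion says that brief-intervention trials on alcohol commonly find "small reductions in alcohol consumption at follow-up also in the control group". Among the possible reasons it lists effects of screening and measurement, unintended advice in the BAU arm, and regression towards the mean.

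**The concern.** A before-after change in one group mixes the effect of the information given with everything else that moves patients over the same period: natural course, response to being screened and measured, and regression to the mean. In a parallel trial both arms carry those other components, and they drop out of the between-arm difference. Patients enter this trial by passing cut-offs of 15 headache days and 10 medication days per month, so some regression to the mean is to be expected in both arms.

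The planning difference is therefore larger than the between-arm difference by whatever change occurs under BAU, unless BI does better than the earlier unstructured information did. The article acknowledges that controls tend to improve, but its sample size paragraph makes no deduction. What is at stake is the meaning of the printed 80% and of the statement that 20 GPs are enough.

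**Working it through.** **Inputs from the article.** Power 80%; 5% level; 18 patients per arm unadjusted; ICC 0.5; 20 GPs with 8 patients each (160 in total); 5 patients per GP as the fallback; half of the CME groups to each arm.

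**Assumptions.** Two-sided test (the article does not say); 10 GPs per arm; BI produces the same change as the earlier study. The BAU change is a share *f* of that change, with *f* from 0 to 50%. The article gives no figure for *f*, and no mean or SD from the source study.

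**Step 1: the plan's own figure.** Without a mean and SD, 18 per arm cannot be derived forwards, so I solved backwards. A two-sample t-test with 18 per arm, 80% power and two-sided 5% needs a standardised difference d = 0.961. The normal formula, (1.960 + 0.842) × √(2/18), gives 0.934. The adopted total is consistent with 18 per arm at the stated ICC: design effect 1 + (8 − 1) × 0.5 = 4.5, then 18 × 4.5 = 81 per arm, or 162 against the stated 160.

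**Step 2: allow for BAU change at 18 per arm.** The between-arm difference becomes d × (1 − f).

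| f | difference (SD) | power at 18 per arm | independent patients per arm for 80% |
|---|---|---|---|
| 0 | 0.961 | 80% | 18 |
| 10% | 0.865 | 71% | 22 |
| 25% | 0.721 | 56% | 32 |
| 50% | 0.481 | 29% | 69 |

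**Step 3: the adopted 160 patients.** The effective number per arm is 80 / (1 + 7 × ICC): 80/4.5 = 17.8 at ICC 0.5, 80/2.4 = 33.3 at 0.2, and 80/1.7 = 47.1 at 0.1.

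| f | ICC 0.5 | ICC 0.2 | ICC 0.1 |
|---|---|---|---|
| 0 | 79.5% | 97% | over 99% |
| 10% | 71% | 94% | 99% |
| 25% | 55% | 83% | 93% |
| 50% | 29% | 49% | 64% |

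**Step 4: five patients per GP.** At ICC 0.5 the design effect is 1 + 4 × 0.5 = 3, so 50 per arm is worth 16.7. Power is 77% with no BAU change, 52% at f = 25% and 27% at f = 50%.

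**Step 5: is BAU change covered elsewhere?** The section gives two reasons for going to 20 GPs: the unknown ICC and carry-over between GP groups. Step 1 shows that at ICC 0.5 clustering alone uses up all 160 patients. Nothing is left at that value for carry-over or for any other improvement under BAU.

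**The case against.** Several points on the other side stand.

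- The loss of power depends on BI doing no better than the earlier unstructured information. BI adds a dependence score, feedback and individual advice. If BI achieves (1 + f) times the earlier change, the difference is again d and the 80% is restored. A reader might infer that the 80% holds only if BAU patients do not improve at all; that is too strong.
- The 80% is attached to 18 unadjusted patients per arm. The section gives no power for 160, calls its work an approximation, and labels the ICC of 0.5 a worst case. At lower ICCs there is real slack, as Step 3 shows. A reader might infer that the trial is underpowered; the article does not establish that.
- The Discussion speaks of small reductions in controls and describes measures to limit them: blinding, embedding the medication questions among others, and withholding the dependence scale from BAU patients until three months. The 50% share is a stress value, not something the article predicts. These measures address assessment effects, however, and do not remove regression to the mean.
- There is no slip in the arithmetic, since the stated ICC reproduces 160 closely. The fault is in which quantity was used as the difference.

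Three further inferences are tempting and should not be drawn. One could recompute the proportion calculation from a starting value of 100% with frequent headache, but the article gives neither the before nor the after proportion and does not say whether 30 is per arm, so any such figure is guesswork. One could dilute the effect for BI patients who never attend the consultation, but no attendance rate is given. One could say that a null result would tell nothing against BI, but that reading will rest on the 95% confidence intervals that the Statistics section plans, not on planning power.

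**Conclusion.** The point holds in a limited form. The medication-days calculation uses an uncontrolled before-after change as the BI-BAU difference and deducts nothing for BAU, against the article's own expectation that controls improve. If BI equals the earlier change, a BAU change of a quarter of it takes power from 80% to about 56% at 18 per arm, and to about 55% for 160 patients at the plan's worst-case ICC. At an ICC of 0.1 or 0.2 the same BAU change leaves 93% or 83%. So adequacy turns on two unknowns, BAU change and ICC, and the article allows for only the second. Calling 160 patients reasonably safe is not supported under the worst case that the section itself sets.

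The proportion calculation draws on the same before-after source and has the same weakness in kind, but its size cannot be worked out from the article. The matter should be corrected. It does not touch the design, the randomisation or the analysis.

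**What to change.** Rewrite the power paragraph so that it:

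- states the assumed change under BI, the assumed change under BAU and the SD separately, with the source of each, and whether the test is two-sided;
- powers the trial on the difference between the two changes;
- shows power, or the smallest detectable BI-BAU difference, for 20 GPs with 8 and with 5 patients each, over a range of BAU change (for example 0, 10%, 25% and 50% of the earlier change) and of ICC (for example 0.1, 0.2 and 0.5);
- restates the proportion calculation in the same way, as a BI proportion against a BAU proportion at three months, and says whether its patient count is per arm;
- qualifies the statement that the size is reasonably safe by the BAU change and ICC under which it is true.

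The cost is one rewritten paragraph, with a less favourable figure at the worst-case ICC. No additional patients or GPs are needed to make the change.

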#### Statistics

All analyses will be focused at the patient level (inference unit will be patient). We will perform a series of frequency analyses tabulating outcome variables against various explanatory variables and/or confounders. Suitable descriptive statistics will be used. Since individual observations within the same cluster (ie. patients of one GP) may be correlated, the intra-cluster (intra-class) correlation coefficient (ICC) measuring such a “clustering effect” and estimating the relative variability within and between clusters will be calculated for both intervention- and control groups. Analysis of differences between BI- and BAU groups based on mixed linear models (MLM) will be performed to account for the hierarchical nature of data, where the main point is to allow variation to be modelled at each level of the data, for example, the GP and the patient level. 95% confidence intervals will be used.

Analysis based on prespecified hypotheses regarding the two primary and the secondary outcomes will be performed as hypothesis testing on the entire dataset and Bonferroni corrections will be used for multiple comparisons. For evaluation of possible outcome predictors where no prior data from this population exist, split file analysis 
[103] will be used. The splitting of the data set will be performed prior to any analyses of primary and/or secondary outcomes.

The intention-to-treat principle will be followed by including all patients with at least one follow-up response. Missing values will be handled using multiple imputation techniques.

SPSS 16.0 and SAS will be used for statistical analyses.

Registration of electronic data from the semi-structured interviews will be done by using Snap Survey (Snap Survey, London, UK).

The participating patients will receive a weekly reminder regarding the headache diary via mobile phone (SMS) during each two weeks diary period at three, six and twelve months, respectively.

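### The sample size is worked out at the 5% level and makes no allowance for the Bonferroni correction planned for the primary outcomes, so the stated 80% power is not that of the planned test

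*Protocol article*

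**What the plan says.** The Power calculations section of the protocol article starts from "Using 80% power for the detection of a similar sized difference as found in the previous study for number of days of medication intake". It concludes that "we would need 18 patients in each arm unadjusted", or "five clusters (ie. GPs) with eight patients each, to achieve significant results at the 5% level". It gives neither the difference nor its standard deviation, only a reference to an earlier study.

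The ICC is unknown and is "here estimated at 0.5 as a “worst case". For that reason, and because carry-over between groups of GPs is also unknown, the section adopts 20 GPs and 160 patients. It adds that five patients per GP would still be enough at the 5% level. No power is stated for the adopted sample.

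Outcome measures and Table 3 give two primary outcome variables at three months: headache days and medication days per month. The Statistics section plans hypothesis tests on the two primary and the secondary outcomes and says that "Bonferroni corrections will be used for multiple comparisons". It does not say how many comparisons the correction covers.

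**The concern.** A power figure describes one test at one threshold. Here the threshold in the sample size section (5%) is not the one in the analysis section (5% divided by some number of comparisons). The enlargement to 160 patients was not made for this reason: ICC and carry-over are the only grounds given.

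Two things depend on it. The first is the claim that 160 patients, or 100 with five per GP, are enough. The second is the decision described under Ethics and data security, where GPs in the control arm may be offered the intervention course if the main three-month outcomes are significantly better with the intervention. Readers should know which threshold defines significance and what chance the trial has of reaching it.

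**Working it through.** **Inputs from the protocol.** 18 per arm unadjusted; 80% power; 5% level; ICC 0.5; 20 GPs with eight patients each (fallback five); half of the CME groups in each arm, taken here as 10 GPs per arm; two primary outcome variables.

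**Assumptions.** Two-sided tests, because sidedness is not stated. The effect size is back-solved, so the 18 per arm is taken as given and is not independently confirmed. The Bonferroni family is two, giving 0.05/2 = 0.025. No loss to carry-over.

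**Step 1: effect implied by 18 per arm.** By the normal formula, d = √(2/18) × (1.960 + 0.842) = 0.934. With the t-test, d = 0.961. Both return 80% at 18 per arm and alpha 0.05.

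**Step 2: same patients at alpha 0.025.** Power ≈ Φ(d√(n/2) − z). Here d√(18/2) = 2.802, and 2.802 − 2.241 ≈ 0.56, so power is 71.2%; the t-test gives 70.4%. To recover 80%, n must rise by ((2.241 + 0.842)/(1.960 + 0.842))² = 1.211, and 18 × 1.211 = 21.8, so 22 per arm.

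**Step 3: the adopted sample.** The design effect is 1 + (m − 1) × ICC. For m = 8 and ICC 0.5 it is 1 + 7 × 0.5 = 4.5. Then 18 × 4.5 = 81 per arm, which is almost exactly the 80 per arm adopted. So the 160 patients are what the 5% level requires at ICC 0.5, with nothing spare. The effective size is 80/4.5 = 17.8 per arm. For m = 5 the design effect is 1 + 4 × 0.5 = 3.0 and the effective size is 50/3.0 = 16.7 per arm.

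| Patients per GP | ICC | Effective n per arm | Power at 0.05 (normal / t) | Power at 0.025 (normal / t) |
|---|---|---|---|---|
| 8 | 0.5 | 17.8 | 79.5% / 79.5% | 70.6% / 69.7% |
| 8 | 0.4 | 21.1 | 85.8% / 86.1% | 78.5% / 78.2% |
| 8 | 0.38 | 21.9 | 87.0% / 87.4% | 80.1% / 80.0% |
| 8 | 0.3 | 25.8 | 91.8% / 92.3% | 86.7% / 86.9% |
| 8 | 0.2 | 33.3 | 96.8% / 97.2% | 94.2% / 94.6% |
| 5 | 0.5 | 16.7 | 76.9% / 76.7% | 67.5% / 66.3% |

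The t figures use 2n − 2 degrees of freedom with n the effective size. With 18 degrees of freedom, for 20 GPs, the first row becomes 77.4% and 66.4%.

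**Step 4: a wider family.** Table 3 lists four primary rows: two between-arm differences and two changes from baseline. Counting four gives alpha 0.0125. Power at 18 per arm is then 61.9% (normal) or 60.0% (t). For 160 patients at ICC 0.5 it is 61.3% or 59.3%.

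**The case against.** The strongest reply is that the 80% was never claimed for the trial as it will be run. It belongs to the minimum, 18 per arm or five GPs with eight patients each, and the trial enrols 20 GPs. ICC 0.5 is the protocol's own worst case. The five-cluster figure, if it is per arm, implies a design effect of 40/18 = 2.22 and so an ICC of (2.22 − 1)/7 = 0.17. At that value 160 patients give about 96% power at alpha 0.025. This stands: a reader might infer that the trial is underpowered at about 70% whatever the ICC, and the protocol does not support that. It does not remove the point, because 0.5 is the only ICC the protocol states and at 0.5 the enlarged sample leaves no margin.

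A second reply is that 0.025 is an assumption. It is. A family of two is the mildest reading of a correction applied to the two primary outcomes, and any larger family gives lower power.

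Three further inferences are tempting and should be resisted.
- That the second calculation ("For analysis of the proportion of patients with more than 15 days of headache, power calculations yield 30 patients or eight clusters (GPs) with eight" per GP) needs the same inflation. It concerns the proportion with more than 15 headache days, which is not a primary outcome, and the proportions behind it are not given.
- That "95% confidence intervals will be used" is a separate error. A 95% interval can exclude zero while the corrected test is not significant, but reporting unadjusted intervals beside corrected tests is common and is a reporting choice.
- That more patients must be recruited. This would follow only if the ICC were known to be near 0.5.

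**Conclusion.** The point holds in a conditional form. The threshold used to size the trial is not the threshold planned for the primary tests, and nothing in the power section allows for the difference. At 18 per arm the stated 80% becomes about 70%. For the adopted 20 GPs with eight patients each, power at ICC 0.5 is about 70% instead of about 80%; with five patients per GP it is about 66–68%. At eight per GP it is about 78% at ICC 0.4, 80% at about 0.38, 87% at 0.3 and 95% at 0.2.

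These figures rest on two-sided testing, the back-solved difference of about 0.96 (0.93 by the normal formula), equal arms, a family of two and no dilution from carry-over. The mismatch itself does not depend on the exact values. It corrects a figure that the trial relies on, but it does not invalidate the design.

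**What to change.** In the Statistics section, state how many comparisons the primary Bonferroni family contains. In the Power calculations section, restate the power of the adopted 20 GPs at the resulting alpha, with eight and with five patients per GP, over a range of ICCs that includes 0.5. State the assumed difference, its standard deviation and the sidedness alongside, so that the figure can be checked.

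This changes text only and leaves enrolment as it is. The cost is a less favourable stated power at the worst-case ICC.
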